### 2.1. Study Design and Participants

The participants will be recruited in PD outpatient’s clinic of the Beata María Ana Hospital of Madrid, Spain. The subjects included will be assessed by a neurologist expert in movement disorders. All patients will be idiopathic PD patients diagnosed according to the UK Parkinson’s Disease Society Brain Bank criteria who suffer from whatever PD-related pain, determined by The Parkinson’s Disease Pain Classification System (PDPCS) [33] and with a pain intensity of 3 out 10 points in the Visual Analogue Scale (VAS) while in ON state, that is, when levodopa is acting. The rest of specific inclusion criteria and the exclusion ones are listed in Table 1 and Table 2. During the protocol, changes in analgesic medication during in the previous week or PD treatment in the previous month will be forbidden and if necessary, will lead to exclusion of the patient. Informed consent for all included procedures (therapies and outcomes measurement), approved by the ethics committee, will be obtained from all subjects before their inclusion, and both studies will follow the principles outlined in the Declaration of Helsinki.

Sensitive data for all participants will be registered separately, anonymized, and guarded according to current data protection European laws. All data will be registered and double checked in a database designed specifically for the studies.

Recruitment in both protocols will be made so placebo and active groups will be matched by age and the recruitment will be stratified in groups of subjects younger than 60 years and older than 60, always ensuring that there is an equitable number of subjects in the two sections.

It is well known that there are gender differences in pain thresholds in healthy humans [34] and some evidence suggests that greater disease severity, female gender and higher doses of mediation are associated with greater pain intensity in PD [35]. For this reason, inclusion of at least one third of female subjects will be assured. Disease severity and total dopaminergic daily dose will be controlled in the final analysis of results.

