#### 2.1.1. tDCS-Based Study

This study will be a triple-blinded experimental longitudinal prospective randomized controlled trial with a parallel design. The randomization will be realized through the GraphPad software (GraphPad Software, San Diego, C.A., U.S.A.), by an independent investigator. All the participants who fulfill the inclusion criteria and have none of the exclusion one will be randomly allocated in two groups: active-tDCS (a-tDCS) or sham-tDCS (s-tDCS). Allocation concealment will be ensured by the inclusion of the assigned group in closed opaque envelopes that will be opened at the time of the intervention. Triple-blind criteria will be achieved by identic collocation of the electrodes in both groups and by activating the “double-blind” option in the Starstim tCS^®^ Software (Neuroelectrics Inc, Barcelona, Spain) that allows the protocol to be concealed by writing a neutral number. The investigator in charge of concealing allocation will also conceal the protocols with the neutral number and the therapist will read it in the envelope, ignoring which number coincides with each intervention. At the end of the full treatment, patients will be asked about which stimulation condition they think they received and how confident they are in their guess. After each session a tDCS adverse effects questionnaire will be applied, the patient will be asked about any symptoms that they have experienced during the session in order to be able to identify possible adverse effects not described. In addition, their comfort will be assessed using a specific comfort questionnaire specified in the protocol section. These questionnaires will be necessary to obtain quantitative information on tDCS tolerability and blinding maintenance, which is scarce in PD patients [36]. Patients recruited will not meet in waiting rooms to avoid them to comment on their experience during the protocol. The statistician will be also blinded through the mentioned neutral numbers. Unblinding will be permissible in any event where it could pose a risk for the patient’s health. The Institutional Research Committee and Institutional Ethics Committee of Hospital Universitario 12 de Octubre approved this study with code 20-515 on December 2020 and the trial was registered in www.clinicaltrials.gov number NCT04651699.

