### 2.4. Sample Size Calculation

#### 2.4.1. tDCS-Based Study

The simple size for the tDCS-based study was calculated using G*Power software (version 2.1, Heinrich-Heine-Universität Düsseldorf, Düsseldorf, Germany), taking into consideration the design of two intervention groups and three assessment times. The primary outcome was chosen to be King’s Parkinson’s Disease Pain Scale with an estimated effect size of F = 0.25. An α level of 0.05 and a power of 90% was assumed, with a total sample of 28 subjects estimated. Considering a 15% follow-up loss, we estimated a minimal sample size of 32 patients, with a minimal recruitment of 16 required for each of the intervention groups.

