### 2.5. Data Analyses

The SPSS software package (version 25.00; SPSS inc., Chicago, IL, USA) will be used by a blinded statistician for statistical analysis of the data. Demographic and clinical variables will be presented as mean and standard deviation. A 95% confidence interval (CI) will be taken, considering statistically significant all those values that had a *p* < 0.05. Parametric statistical tests will be used for hypothesis testing (*n* > 30). To show differences in the main variables, an analysis of variance (ANOVA) 2 × 3 of repeated measurements will be carried out taking time and group as factors, being the groups active-tDCS (a-tDCS) vs. sham-tDCS (s-tDCS) in the tDCS-based study and AO+MI-BCI vs. AO-control AO+MI-based study, and the measurements times pre-treatment, post-treatment, and at 15 days post-treatment. If significant differences are found in any of the interactions, a post hoc analysis will be performed with Bonferroni correction. The effect sizes will be calculated by means of the d of Cohen, being classified as small (d between 0.20 and 0.49), medium (d between 0.50 and 0.79), or large (d greater than 0.80) following the method of Cohen.

For the rest of the psychological variables, a Pearson’s correlation with the physical variables will be carried out in order to find relationships between both. Low correlation will be taken as that with values between 0.2 and 0.39; the correlation will be considered moderate when the value goes from 0.40 to 0.79; and high when the value of the correlation is greater than 0.80.

For the analysis of neurophysiological variables rMT, MEP magnitudes will be determined by averaging peak-to peak amplitudes. The ratio of the rMT, MEP amplitude recorded at each post-intervention time-point relative to the baseline rMT will be calculated [(MEP amplitude at each stage–baseline MEP amplitude)/baseline MEP amplitude Å~100]. Statistical analyses will be performed on the calculated test-to baseline MEP ratios. For the CSP values the time will be measured manually in each trial and averaged and the ratio compared to baseline measurement will be also calculated.

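### Sex is named with disease severity and medication dose as a correlate of pain, but is answered only by an enrolment quota and is left off the list of factors to be controlled in the analysis

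*Protocol article*

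**What the plan says.** Section 2.1 of the protocol article gives two reasons for attending to sex. The first concerns thresholds: "It is well known that there are gender differences in pain thresholds in healthy humans". The second concerns the disease itself: "some evidence suggests that greater disease severity, female gender and higher doses of mediation are associated with greater pain intensity in PD".

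The response to sex is "For this reason, inclusion of at least one third of female subjects will be assured". The next sentence deals with the other two factors: "Disease severity and total dopaminergic daily dose will be controlled in the final analysis of results". Sex is not in that sentence.

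Age is handled separately in the same section, with a single cut at 60 years: "placebo and active groups will be matched by age and the recruitment will be stratified in groups of subjects younger than 60 years and older". No other matching or stratification factor is named.

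Section 2.1.1 describes the allocation for the tDCS trial: "The randomization will be realized through the GraphPad software (GraphPad Software, San Diego, C.A., U.S.A.), by an independent investigator". Section 2.1.2 uses the same software for the AO+MI trial. Neither section mentions a sex stratum. Section 2.5 sets the main analysis as an "analysis of variance (ANOVA) 2 × 3 of repeated measurements will be carried out taking time and group as factors". The regression and ON/OFF analyses in the same section do not name sex. Section 2.6 proposes a comparison of mean reduction in the King's scale (KPDPS) between the two protocols, with no adjustment for sex stated.

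**The concern.** The reason and the remedy do not match. If sex is raised because it goes with pain, the statistical response is to balance it between arms or adjust for it. A floor on the number of women does neither. It governs who enters the trial and secures some representation of women, but says nothing about how many fall in each arm. Of the three correlates named in one sentence, two get analytic control and the third does not.

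At stake is precision and interpretability in trials of 16 per arm. If a visible sex imbalance arises, the investigators will have no prespecified way of handling it and may be tempted to adjust after seeing the data. The comparison between the two trials is more exposed. Patients are randomised within each trial, and the quota is only a minimum, so the two samples may differ in their proportion of women.

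**Working it through.** **Inputs**
- Total per trial 32, with 16 per arm (Sections 2.4.1 and 2.4.2).
- Quota of at least one third women: 32/3 = 10.7, so at least 11 women. It is stated for the sample, not per arm.
- No sex stratum (Sections 2.1, 2.1.1 and 2.1.2).
- Assumption: allocation ends exactly 16:16 and is unrelated to sex. The one age stratum is ignored, since its relation to sex is not given.

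The plan gives no figure of its own for sex balance, so there is none to reproduce.

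**Step 1. Chance of an uneven split, quota just met**

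Let X be the number of women in one arm. Then P(X = x) = C(11, x) × C(21, 16 − x) / C(32, 16), with C(32, 16) = 601,080,390.

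| Split of 11 women | Probability, both directions |
|---|---|
| 6:5 | 2 × 0.2711 = 0.542 |
| 7:4 | 2 × 0.1614 = 0.323 |
| 8:3 | 2 × 0.0559 = 0.112 |
| 9:2 or worse | 0.023 |

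- 7:4 or worse: 1 − 0.542 = 0.458. This sounds large, but 6:5 is the best split possible and 7:4 is one woman away from it.
- 8:3 or worse: 0.112 + 0.023 = 0.135. At 8:3 the arms are 50% and 19% female.

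**Step 2. Sensitivity to the number of women**

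The quota is a floor. With 16 women of 32, the same calculation gives 0.289 for a gap of 4 or more (10:6 or worse) and 0.076 for a gap of 6 or more (11:5 or worse). The standard deviation of the between-arm difference in the share of women is about 17 percentage points with 11 women and 18 with 16.

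**Step 3. Does an imbalance reach the planned test?**

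Let p1 and p2 be the shares of women in the two arms, and b(t) the sex difference in the outcome at time t.
- Contribution of sex to the arm difference at one time point: b(t) × (p1 − p2).
- Contribution to the arm difference in change from baseline: [b(t) − b(0)] × (p1 − p2).

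If b is constant over time, the second expression is zero when the same patients contribute at every visit. The group-by-time interaction and the change scores are then untouched, however uneven the split. If sex predicts change, the second expression is not zero.

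The imbalance can therefore matter where sex predicts change and in comparisons at a single time point. Section 2.6 has the same structure, with p1 and p2 now the shares of women in the two trials. It compares reductions, so it too is affected only if sex predicts change, but there randomisation does not balance sex even in expectation.

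The documents give no value for b(t) and no correlation between sex and change, so the effect on any result cannot be sized.

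**The case against.** Four points can be made on the other side.

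1. Randomisation balances sex in expectation, and the test's error rate and confidence interval already allow for chance imbalance. This stands: there is no systematic bias within either trial.
2. The main analysis concerns change over time, and Section 2.1 cites only differences in level (thresholds in healthy people, pain intensity in the disease). This stands too. A reader might infer that an 8:3 split carries 5/16 = 0.31 of any sex difference into the treatment effect. The documents do not support that in general. It holds for a contrast at one time point, or where the sex difference is a difference in change.
3. A reader might also infer that the protocol says most of its main outcomes differ by sex. It does not. It speaks of pain thresholds in healthy people and of pain intensity in the disease, the latter hedged as some evidence of association. It makes no such statement about temporal summation or conditioned pain modulation.
4. An article may leave the full covariate list to an analysis plan, and the sentence on severity and dose is not presented as exhaustive. This carries some weight, and the analysis plan may already include sex. But Section 2.1 itself takes up these three correlates, says which will be controlled, and gives the third a different remedy that cannot do the same job. That is a stated choice and not an omitted detail.

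**Conclusion.** The point holds at low severity. The quota cannot balance or adjust for sex between arms, and nothing elsewhere in the article does so. With the quota just met and 16:16 allocation without a sex stratum, a split of 8:3 or worse has probability 0.135 in each trial. About 86% of allocations would do better. The two trials are randomised and analysed separately, so the figure should be read for each one alone.

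The consequence is chance imbalance and possible loss of precision. It is confined to situations where sex predicts change and to comparisons at a single time point. The cross-trial comparison of KPDPS reduction is a further case, because the sex mix may differ between trials. The findings do not show that either trial's treatment comparison would be biased, nor that allocation must be stratified by sex. Four age-by-sex strata in 32 patients would be sparse, and covariate adjustment avoids that.

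**What to change.** Keep the one-third quota and describe its purpose as representativeness. In Section 2.1, add sex to the factors to be controlled, beside disease severity and total dopaminergic daily dose. In Section 2.5, name sex as a prespecified covariate in the main-outcome models, entered with its interaction with time, since a sex term for level alone does not alter the group-by-time test. In Section 2.6, name it as a covariate in the cross-trial comparison of KPDPS reduction. State whether the quota applies to the whole sample or to each arm. If the analysis plan already adjusts for sex, the article and the plan need only be brought into agreement.

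The cost is one between-subject degree of freedom: with 32 patients and two groups the between-subject error falls from 32 − 2 = 30 to 29. The within-subject error for three visits falls from 30 × 2 = 60 to 29 × 2 = 58. No new data are needed, because sex has to be recorded for the quota to operate. The randomisation list need not change.

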#### 2.1.1. tDCS-Based Study

This study will be a triple-blinded experimental longitudinal prospective randomized controlled trial with a parallel design. The randomization will be realized through the GraphPad software (GraphPad Software, San Diego, C.A., U.S.A.), by an independent investigator. All the participants who fulfill the inclusion criteria and have none of the exclusion one will be randomly allocated in two groups: active-tDCS (a-tDCS) or sham-tDCS (s-tDCS). Allocation concealment will be ensured by the inclusion of the assigned group in closed opaque envelopes that will be opened at the time of the intervention. Triple-blind criteria will be achieved by identic collocation of the electrodes in both groups and by activating the “double-blind” option in the Starstim tCS^®^ Software (Neuroelectrics Inc, Barcelona, Spain) that allows the protocol to be concealed by writing a neutral number. The investigator in charge of concealing allocation will also conceal the protocols with the neutral number and the therapist will read it in the envelope, ignoring which number coincides with each intervention. At the end of the full treatment, patients will be asked about which stimulation condition they think they received and how confident they are in their guess. After each session a tDCS adverse effects questionnaire will be applied, the patient will be asked about any symptoms that they have experienced during the session in order to be able to identify possible adverse effects not described. In addition, their comfort will be assessed using a specific comfort questionnaire specified in the protocol section. These questionnaires will be necessary to obtain quantitative information on tDCS tolerability and blinding maintenance, which is scarce in PD patients [36]. Patients recruited will not meet in waiting rooms to avoid them to comment on their experience during the protocol. The statistician will be also blinded through the mentioned neutral numbers. Unblinding will be permissible in any event where it could pose a risk for the patient’s health. The Institutional Research Committee and Institutional Ethics Committee of Hospital Universitario 12 de Octubre approved this study with code 20-515 on December 2020 and the trial was registered in www.clinicaltrials.gov number NCT04651699.

#### 2.1.2. AO+MI-Based Study

This study will be a double-blinded experimental longitudinal prospective randomized controlled trial with a parallel design. The randomization will be realized through the GraphPad software (GraphPad Software, Inc CA 92037 EE.UU.). All the participants who fulfil the inclusion criteria and have none of the exclusion one will be randomly allocated in two groups: AO+MI through a Brain-Computer Interface (BCI) training paradigm in Virtual Reality (VR) (or neurogame) (AO+MI-BCI) or AO of non-related with movement illustrations (AO-control). Allocation concealment will be ensured by the inclusion of the assigned group in closed opaque envelopes that will be opened at the time of the intervention. Double-blind criteria will be achieved by following the same protocol with the same instruments in both groups. The evaluator will not be able to stay in the same room during the intervention and patients will not know the instructions and specific hypothesis of each protocol. The statistician will be blinded through the assignment of neutral numbers to both groups. Patients recruited will not meet in waiting rooms to avoid them to comment on their experience during the protocol. Unblinding will be permissible when any event could suppose a risk for the patient’s health. The Institutional Research Committee and Institutional Ethics Committee of Hospital Universitario 12 de Octubre approved this study with code 20-514 on December 2020 and the trial was registered in Clinical Trial, NCT04651478.

### 2.2. Intervention Protocols

In both studies, PD patients, independently of the group allocation, will undergo 10 sessions in two weeks (Monday to Friday). All sessions will be performed during ON state of patients and with their usual analgesic medication, to ensure their comfort.

#### 2.2.1. tDCS-Based Study

The Starstim tDCS^®^ stimulator (Neuroelectrics, Barcelona, Spain) will be used by an experienced physical therapist to transfer the direct current by a saline-soak pair of surface sponge electrodes (35 cm^2^).

In the experimental group (a-tDCS), the anode electrode will be placed over C3 (EEG 10/20 system) and the cathode electrode over the contralateral supraorbital area (Fp2), in order to enhance excitability of M1 [37]. Regarding the stimulated hemisphere, contralateral M1 will be stimulated in patients with asymmetric pain [38] but in patients with symmetric pain, the left hemisphere will be targeted due to the widespread changes induced by tDCS in other cortical areas, including contralateral M1 [26]. A constant current of 2 mA intensity (subthreshold intensity) will be applied for 20 min [39], with 30 s of ramp-up and 30 s of ramp-down.

For the sham stimulation (s-tCDS), the electrodes will be placed in the same positions as for M1 stimulation, but only applying ramping active current for 30 s in the beginning and at the end of the procedure for a reliable blinding [40].

During interventions, all subjects will be seated in a relaxed position in spite of this technique have demonstrated to be safe and pleasant [41]. When “on demand” analgesic medication is part of the usual treatment of the patient, the daily doses used will be registered to follow the short-term efficacy of the protocol. Our protocol follows the security and replicability recommendations for the use of this technique [42]. Possible adverse effects [41] will be assessed after each session by the Comfort Rating Questionnaire (CRQ), a modified version of the unpublished questionnaire from the Göttingen study group [43,44], and its apparition could lead in the interruption of the intervention. Although no severe adverse effects are expected. Any adverse effect will be notified to a licensed medical doctor. Management of possible adverse effects will be individualized and according to the severity. In case of headache or scalp pain, an extra dose of analgesics will be prescribed if necessary and recorded for each patient, in case of skin local reactions such as reddening or itching local application of talcum will be suggested. In case of sleep changes, concentration problems, mood changes, or any other non-previously described adverse effects detected in the daily post treatment assessment will be managed individually and in case of persistence the medical doctor will make the decision to suspend the protocol for the patient and set a follow-up until the symptoms are resolved.

#### 2.2.2. AO+MI-Based Study

The experimental group will follow three stages to complete each session:

Firstly, an experienced technician will acquire EEG through a BCIs system with 32 active electrodes equipped with a low-noise biosignal amplifier and a 24-bit A/D converter at 256 Hz (LiveAmp 8 biosignal amplifier, Brain Products GmbH, Gilching, Germany). The spatial distribution of the electrodes will cover primarily the motor and somatosensory areas of the brain. Specifically, the Frontal-Central (FC3, FC4), Central (C1, C2, C3, C4), and Central-Parietal (CP3, CP4) in a small Laplacian configuration for spatial filtering. EEG data acquisition and processing will be performed through the OpenVibe platform [45], which will transmit the data to the RehabNet Control Panel (Reh@Panel) [46] via the Lab Streaming Layer (LSL) (https://github.com/sccn/labstreaminglayer) protocol to control the virtual environment.

Secondly, the BCIs training protocol will be designed and adapted based on the Graz-BCI paradigm [47]. The first step will be the acquisition of the raw EEG data in order to extract features to train a classifier to distinguish Right and Left imagined hand movements. Thus, the patient will have to perform mental imagery of the corresponding hand, based on the presented stimuli in the screen. The training session will be configured to acquire data in 24 blocks per class (Right- or Left-hand imagery) in a randomized order. Afterwards, the data will be filtered both spatially and temporarily between the Alpha and Beta bands (8–30 Hz) for creating the feature vector to be used to train a Linear Discriminant Analysis (LDA) classifier.

Finally, patients will undergo the treatment itself through the NeuRow platform [48]. NeuRow is a gamified BCI training paradigm in VR (or neurogame) that allows patients to perform the same actions as they would do in real-life. In NeuRow, patients will see a boat and two high fidelity virtual arms gripping two oars in first person view. Patients will have to imagine the movement of each corresponding hand to rotate each oar and progress, observing the movement imagined on screen. The goal of the task is to collect as many flags as possible in a fixed amount of time. In order to improve adherence, the number of flags collected will be recorded in each session. It will be able to adapt the boat speed, turn speed and cut-off angle, to help patients not to deviate in excess from the target. The treatment itself will be performed for 20 min each session [49], divided in 4 series of 5 min to prevent fatigue. It is considered a multiplatform virtual environment developed in Unity game engine (Unity Technologies, San Francisco, CA, USA) and it has been used already with patients suffering from chronic motor disability [50].

The control group will follow an AO through non-related with movement illustrations protocol each session. The initial protocol will be omitted for being unnecessary. The same configuration will be applied simulating a BCI task, but playing a video about graphic illustrations, people faces and landscapes, never related with human movement. They will address interesting and changing topics to avoid patient’s boredom [51]. The control session will last 20 min, also divided in 4 series of 5 min and the therapist will give the instructions of observe and relax.

During interventions, all subjects will be seated in a relaxed position and whichever severe adverse event could lead in the interruption of the intervention, although they are considered unlikely. When “on demand” analgesic medication is part of the usual treatment of the patient, the daily doses used will be registered to follow the short-term efficacy of the protocol.

Possible adverse effects such as dizziness, mental fatigue, or whichever will be assessed and specifically managed after each session. Any adverse effect will be notified to a licensed medical doctor, although severe adverse effects are not expected, if they appear, the medical doctor will make the decision to suspend the protocol for the patient and set a follow-up until the symptoms are resolved.

